**Study Population:**

**Inclusion Criteria:**

- Continuously followed up by Out Patient Clinic (OPC).
- Age from 10 to 16 years of age (based on date of birth)

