**Indicators for Evaluation:**

The primary endpoint is time to virological treatment failure; the secondary endpoints are time to immunological and clinical treatment failure. In addition adherence will be assessed, risk factors of treatment failure will be evaluated and ART resistance mutations will be assessed. Adverse events including ARV adverse drug reactions, immune reconstruction inflammatory syndrome (IRIS) and OIs development, as well as Death/Mortality will be assessed. Loss of follow-up will be determined after the follow up period for patients who do not attend clinical visits and laboratory monitoring and will be analyzed as death. According to intention to treat patients that are absent one or more follow up visits and then turn up will be included in the analysis. Cost effectiveness will be assessed if there is a significant difference after two years follow up between the intervention and control group using costing analysis.

| No. | Indicator | Method of measurement | Method of assessment |
| --- | --- | --- | --- |
| 1 | Time to Virological treatment failure  (primary endpoint) | Viral load test:  -Baseline at enrollment  -Every 6 months of follow-up period | Cutoff (1): 1000 cps/ml (International)  - If the viral load Is above the cut off in the first assessment after 6 months of ART, it is defined as primary virological treatment failure, if the viral load is first suppressed and then detectable, it is referred as secondary virological treatment failure. |
| 2 | Time to Immunological treatment failure (secondary endpoint) | CD4 count:  - Recent result or baseline at enrollment.  Not part of routine follow up but if indicated due to virologic failure. | *Cutoff : below the level of severe immunodeficiency by age  -Child<11 months: % CD4<25%  -12 month <Child<35 months: %CD4<20%  - 35 months <Child<5 years: %CD4<15%  -Child>5 years: CD4 < 100 cell/mm3  *CD4 count falls to or below cutoff after initial recovery response (1). OR CD4 count falls rapidly below cutoff by age as confirmed by at least 2 consecutive times (2). OR CD4 count falls below more than 50% of the peak level during ARV treatment (3).  Decide %, the time length leading to immunological treatment failure in both group (EST & CT) |

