| 3 | Clinical treatment failure (tertiary endpoint) | - Physical exam  - WHO scale in infant development (weight, height, physically active) | - Lack of or decline growth rate in children who initially respond to treatment (1).  - Loss of neurodevelopmental milestone or development of encephalopathy (2).  - Occurrence of new OIs or malignancies or recurrence of bacterial or fungal infections that refractory to treatment (3).  Decide %, the time length leading to clinical treatment failure in both group (EST & CT) |
| 4 | Adherence assessment | - Interview  - Questionnaire  - Pill count  - Pharmacy record | * Cut-off: (Good > 95%, Poor <95%)  - Good adherence: > 95% doses taken on time  - Poor adherence: < 95% doses taken OR > 95% doses taken but not on time.  * Other factors related:  - On time at every check-up visit  - Same caretaker at every check-up visit  - The current belief of caretaker to ART  - The current collaboration of child to ART  Decide % adherence in both group (EST & CT) |
| 5 | Risk factors of treatment failure | - Questionnaire  - Counseling | - Decide the pattern of risk factors of both groups and compare. |
| 6 | ART mutation assessment | - Genotyping (sequencing or real-time PCR for specific allele) | * ART mutation assessment for patients that have detectable viral load above 1000 copies/ml  * Baseline resistance will be assessed in a subsample of the cohort.  * Compare to Stanford HIV mutations database regarding to the regimens that patients were treated.  Decide pattern of mutation, % in both group (EST & CT) |
| 7 | ARV adverse effects | - Physical exam  - Lab test (enzyme) | Decide % of children having ARV adverse effects from both group (EST and CT) |
| 8 | IRIS | - Physical exam | Decide % of children having IRIS from both group (EST and CT) |
| 9 | OIs development | - Physical exam | Decide % of children having OIs development from both group (EST and CT) |
| 10 | Death/Mortality | - Regardless death causes | Decide % of children death from both group (EST and CT) |
| 11 | Development of AIDS events | - Physical exam | Decide % of children with development of AIDS events from both group (EST and CT) |
| 12 | Loss of follow-up  = Death (in analysis) | - Not able to manage within 6 months. | Assume as death/mortality in analysis.  These patients will be drawn out of study, If they come back to OPC, they will receive support as conventional procedure. |

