## Evaluation

- Primary Endpoint: time to virological treatment failure and /or death and/or AIDS-associated events (clinical treatment failure)

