## Interval Assessments

### Interval history and physical exam

The Procedure of following up both groups EST (every 6 months/24-36 months of follow-u) and CT (as OPC routine procedure according to national guidelines)

- Vital signs and weight
- Physical examination
- Physics development and awareness
- Signs and symptoms of OIs

etc.

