**Peer Support Intervention**

**Follow-up 24 months**

**Analysis**

**Appendix 1 B: Trial Flow Chart for both groups (EST and CT)**

|  |  |  | **24 months follow-up**  **Every 6 months = 6 interval assessment** | | | |
| --- | --- | --- | --- | --- | --- | --- |
| **Event** | **SCR** | **Baseline or enrollment** | **1^st^** | **2^nd^** | **3^rd^** | **4^th^** |
| Informed Consent | x |  |  |  |  |  |
| Inclusion/Exclusion Criteria | x |  |  |  |  |  |
| Medical History | x |  |  |  |  |  |
| Clinical Assessments (vital signs, weight, physical exam) |  | x | x | x | x | x |
| Medication Adherence Assessment (if under ART already) |  | x | x | x | x | x |
| Adverse Event Assessment |  | x | x | x | x | x |
| CBC |  | x | x | x | x | x |
| Liver Enzymes Tests |  | x | x | x | x | x |
| AFB sputum (if available) |  | x | If (indicated) | | | |
| CD4 (if available) |  | x |  |  |  |  |
| Viral load |  | x | x | x | x | x |
| Genotype resistance  (0.5 ml plasma) |  | x | If (indicated) | | | |
| -80 oC Stored plasma  (0.5 ml plasma) |  | x | X | X | x | x |

Volume of Blood sample: 3-4 ml/time, assuming having 1.5 ml of plasma enough for VL, genotypic and storage

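### Clinical treatment failure counts any slowing of growth, with no age or sex reference, in a cohort that enters at 10 to 16 years and is followed up to 18

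*Protocol*

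**What the plan says.** **Definition.** In the Protocol, Indicators for Evaluation, row 3, the first criterion for clinical treatment failure is "Lack of or decline growth rate in children who initially respond to treatment (1". No size of decline, duration, confirmation, or age, sex or puberty standard is attached. The method of measurement is a physical examination and a "WHO scale in infant development (weight, height, physically active").

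**Population.** The inclusion criterion is "Age from 10 to 16 years of age (based on date of birth"). Follow-up is 24 months, and the Rationale for Research Subject Selection expects a maximum age of 18 during the study.

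**Role of the endpoint.** The protocol gives three answers:
- Row 3 is headed "Clinical treatment failure (tertiary endpoint").
- The text above the table says "the secondary endpoints are time to immunological and clinical treatment failure".
- The Evaluation section gives the primary endpoint as "time to virological treatment failure and /or death and/or AIDS-associated events (clinical treatment failure"), and the primary objective in the Synopsis uses the same composite.

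**Measurements scheduled.** The flow chart in Appendix 1B has "Clinical Assessments (vital signs, weight, physical exam") at baseline and at visits 1 to 4. The section Interval history and physical exam has "Vital signs and weight", a physical examination and an item on physical development and awareness that is not explained; the list is left open. Neither place names height. Row 13 (physical development) refers only to normal development, and its assessment cell is empty.

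**The concern.** Growth rate falls after the pubertal spurt and then growth stops. A healthy, virally suppressed adolescent who responded to treatment can therefore satisfy both halves of the criterion, lack of growth and decline in growth rate. The restriction to initial responders limits who can be counted, but not how much slowing is needed.

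Events of this kind have nothing to do with adherence or peer support. If they are ascertained alike in both arms, they add the same background to each, raise both failure rates and shrink the difference the trial is meant to detect. The clinical-failure comparison would then partly measure puberty. The same would hold for the primary comparison if the composite in the Evaluation section is the primary endpoint.

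Row 3 also cannot be applied uniformly unless height is recorded at every visit, and no schedule names it. Secondary objective 3 includes physical development and depends on the same measurement.

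**Working it through.** **Inputs.** Failure of 15% (control) and 10% (intervention) at two years, 80% power, two-sided 5%, 10% loss, about 540 patients (Protocol, Sample size). The fraction f of otherwise event-free children who meet only the growth criterion is not in the documents. It is taken as 5%, 10% and 20% and assumed equal in both arms.

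**The plan's own figure first.** The pooled two-proportion formula is

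n per arm = [z₀.₉₇₅·√(2p̄(1−p̄)) + z₀.₈₀·√(p₁(1−p₁) + p₂(1−p₂))]² / (p₁−p₂)²

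With p₁ = 0.15, p₂ = 0.10 and p̄ = 0.125:

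[1.960·√0.21875 + 0.842·√0.2175]² / 0.05² gives 686 per arm, 1372 in total before loss.

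The stated total of 540 is not reproduced; 270 per arm gives about 42% power. That is a separate problem, and the present point does not depend on it. It does mean that the effect on power is best shown at both sizes.

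**Effect of growth-only events.** A child fails if he or she has another failure event or, having none, meets the growth criterion:

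p′ = p + (1−p)·f

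The difference becomes (p₁−p₂)·(1−f), whatever the underlying rates. At f = 10%:
- control 0.15 + 0.85 × 0.10 = 0.235
- intervention 0.10 + 0.90 × 0.10 = 0.19
- difference 0.045 = 0.05 × 0.90

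| f (assumed) | Control | Intervention | Difference (points) | Risk ratio | Power, 686 per arm | Power, 270 per arm | n per arm for 80%, before loss |
|---|---|---|---|---|---|---|---|
| 0 | 15% | 10% | 5.0 | 0.67 | 80% | 42% | 686 |
| 5% | 19.25% | 14.5% | 4.75 | 0.75 | 65% | 31% | 975 |
| 10% | 23.5% | 19% | 4.5 | 0.81 | 53% | 25% | 1297 |
| 20% | 32% | 28% | 4.0 | 0.875 | 37% | 17% | 2060 |

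The absolute difference shrinks slowly. Power falls faster because the variance rises as well.

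**Which endpoint is affected.** The protocol gives no separate rates for clinical failure, so the table takes 15% vs 10% as the contrast for an endpoint that includes it. For clinical failure alone the factor (1−f) still applies, but the base rates are unknown.

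**Height.** Row 3 names weight and height. The flow chart and the interval-visit text name weight only, although both include a physical examination and the interval text adds a development item. Row 3 and the schedules therefore do not match on the measurement the criterion relies on.

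**The case against.** The case on the other side has four parts.

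1. *Clinicians would not record normal pubertal slowing as treatment failure, and the named WHO scale and row 13 point to normal development.* This limits how often the error would occur, which is why f is only an assumption. It does not rescue the rule. The scale is described as one for infants, row 13 is not linked to row 3, and a time-to-event endpoint that rests on unstated judgement will not be applied alike across centres.

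2. *A z-score cut-off is detail for the statistical analysis plan.* The numerical threshold could be set there. But the protocol already states a rule, and that rule does not suit this age group. Nor can an analysis plan recover heights that were not recorded.

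3. *The primary endpoint may be untouched.* This stands in part. The title and secondary objective 1 name virological failure as primary, and the text above the indicator table and row 3 make clinical failure secondary and tertiary. AIDS events also have their own row 11, so a growth event enters the composite only through the bracketed term in the Evaluation section. A reader might infer that the primary analysis is certainly contaminated; the documents support that only conditionally.

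4. *Height may be taken anyway.* This also stands in part. A reader might infer that only weight is scheduled and that physical development cannot be assessed at all. The physical examination and the development item could include height, so the supportable statement is that height is not named.

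**Conclusion.** The concern holds. Row 3 states a growth criterion that normal adolescent development can meet, and it names an infant scale for children aged 10 to 16 at entry. Under literal application and equal ascertainment, the between-arm difference is multiplied by (1−f): 4.75, 4.5 and 4.0 points instead of 5 at f = 5%, 10% and 20%. The value of f is assumed, and nothing in the documents fixes it. If growth were assessed differently by arm, the result would be bias rather than dilution, and the calculation does not cover that.

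The point affects clinical failure as a secondary or tertiary endpoint under any reading, and the primary endpoint if the composite governs.

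Two stronger readings are not supported:

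- A reader might infer that most of the cohort would be counted as failing. With entry age uniform over 10 to 16, half girls, and assumed peak growth at 12 (girls) and 14 (boys), 100% of girls and 4/6 = 67% of boys are at or past peak by month 24, a mean of 83%. The arithmetic is right, but this is a share past an assumed age, not an event rate. A girl who enters at 10 reaches the assumed peak only at the last visit, and a decline needs at least two growth intervals to be seen.
- A reader might infer that the milestone criterion should also go. Nothing shows that it creates false events, and it shares its item with encephalopathy.

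**What to change.** 1. In row 3, replace the raw growth criterion and the infant scale with a pre-set fall from the child's own baseline in age- and sex-standardised z-score (height-for-age, BMI-for-age). Alternatively, take growth out of clinical failure and keep it only as the physical-development outcome in row 13.
2. Leave the milestone and encephalopathy item as it is.
3. Name height among the clinical assessments at baseline and visits 1 to 4, both in Interval history and physical exam and in Appendix 1B.
4. Report row 13 as change in z-score by arm.
5. Reconcile the role of clinical failure across the Synopsis, the text above the indicator table, row 3 and the Evaluation section, so that it is clear whether it is part of the primary endpoint.

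The cost is wording in rows 3 and 13, one height measurement at visits that already take place, and fewer counted clinical failures.

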## Statistical Considerations

- The statistical analysis mainly consists in the comparison between the two groups ETS and CT with respect to the defined primary and secondary endpoints in relation to the semi-quantitative assessment of adherence (by questionnaire, pill counts, and pharmacy records).
- Standard statistical methods will be used. Hazard/Survival analysis will be conducted including death/loss of follow up as “failure” in the analysis. Intention to treat will be used for analysis.
- Regression models with outcome as the dependent variable and a group indicator together with patient characteristics as independent variables will be the main approach.
- For binary outcomes, logistic regression will be used.
- Attention has to be paid to the particular, often skewed, distributions of variables like viral load. Transformations or the use of non-parametric approaches are likely to be necessary if such measures are not dichotomized and used in linear regression.
- The correlation between drug resistance and adherence will be statistically analysed in order to study whether the basic mechanisms of selective drug pressure result in a concave or bell-shaped resistance – adherence relationship (Friedland and Williams, 1999), for these drugs during ETS or CT in a low-income setting.
- The odds ratios of having or not baseline drug resistance mutations as detected by population and deep (single allele PCR) sequencing on drug resistance development and clinical outcomes during treatment independent of treatment adherence will be evaluated.
- Stratified analysis will be conducted comparing the outcomes among the treatment groups.

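### Row 12 of the indicator table withdraws a child after 6 months out of care and counts the child as dead even on return, against the protocol's own intention-to-treat rule for returners

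*Protocol*

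**What the plan says.** Two places in the protocol's section Indicators for Evaluation deal with children who drop out of contact.

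- **Row 12 of the table.** Loss is defined as "Not able to manage within 6 months". The handling is "Assume as death/mortality in analysis", followed by "These patients will be drawn out of study, If they come back to OPC, they will receive support as conventional procedure".
- **The paragraph above the table.** "Loss of follow-up will be determined after the follow up period", and such children are analysed as deaths. The next sentence invokes intention to treat and says that "patients that are absent one or more follow up visits and then turn up will be included in the analysis".

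Three other sections bear on the point.

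- **Evaluation** gives the primary endpoint as "time to virological treatment failure and /or death and/or AIDS-associated events (clinical treatment failure").
- **Statistical Considerations** says "Hazard/Survival analysis will be conducted including death/loss of follow up as" failure, and "Intention to treat will be used for analysis".
- **Interval laboratory test** and **Appendix 1 B** schedule viral loads every 6 months to month 24 in both groups, with no exception for children who lapse and return.

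**The concern.** A child who is out of contact for longer than 6 months and then comes back falls under both rules. Row 12 has already removed the child and coded a death. The paragraph includes the child in the analysis, and its natural reading is that the child is analysed on what is observed. Nothing says which rule prevails.

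This reaches the primary analysis. Death is part of the composite in the Evaluation section. The Indicators section names virological failure alone as primary, but the survival analysis counts loss as failure, so the imputed event would still enter. Under row 12, a child who is alive, back in clinic and possibly suppressed is a failure. Under the paragraph, the same child may be event-free.

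There is also a conduct question. If sites take the withdrawal in row 12 to end study visits, the child's remaining viral loads may not be collected as study data. An analysis plan written later cannot count on having them.

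**Working it through.** **Which children meet both rules.** Visits fall at months 0, 6, 12, 18 and 24. Row 12 does not say when its 6 months start, so both candidate starting points are shown. Viral loads left include the one at return.

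| Last attended | Returns at | Months since last attended | Months since first missed visit | Viral loads left |
|---|---|---|---|---|
| 0 | 12 | 12 | 6 | 3 |
| 6 | 18 | 12 | 6 | 2 |
| 12 | 24 | 12 | 6 | 1 |
| 0 | 18 | 18 | 12 | 2 |
| 6 | 24 | 18 | 12 | 1 |
| 0 | 24 | 24 | 18 | 1 |

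The first three patterns (one missed visit) exceed 6 months only if the clock starts at the last attended visit. The last three (two or more consecutive missed visits, no contact in between) exceed it on either clock. They also fall within the paragraph's rule, which sets no upper limit on the number of missed visits.

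**Inputs.** The Sample size section gives 10% loss, and 2-year failure of 15% in control (CT) and 10% in intervention (ETS). It states both 540 in total (270 per arm) and 260 per group, so planned loss is 0.10 × 260 = 26 or 0.10 × 270 = 27 children per arm. The protocol attaches no figure to the loss rule itself. The return proportion r and the failure proportion f among returners are not given and are assumed below. All of the planned loss is taken to meet row 12.

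**Failure rate if row 12 is followed** (equal loss, planned rates in children not lost):

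- CT: 0.9 × 15% + 10% = 23.5%
- ETS: 0.9 × 10% + 10% = 19.0%
- Difference: 4.5 points

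**Change if returners are analysed on observed data.** Each arm's rate falls by 0.10 × r × (1 − f). The number of children reclassified is 26 or 27 × r × (1 − f).

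| r | f | Fall in arm rate (points) | Children per arm |
|---|---|---|---|
| 0.25 | 0.80 | 0.5 | 1.3 to 1.35 |
| 0.25 | 0.50 | 1.25 | 3.25 to 3.4 |
| 0.50 | 0.80 | 1.0 | 2.6 to 2.7 |
| 0.50 | 0.50 | 2.5 | 6.5 to 6.75 |
| 0.50 | 0.15 CT / 0.10 ETS | 4.25 / 4.5 | 11.05 to 11.5 / 11.7 to 12.15 |
| 1.00 | 0.15 CT / 0.10 ETS | 8.5 / 9.0 | 22.1 to 22.95 / 23.4 to 24.3 |

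**Difference between arms on observed data, equal loss and return:**

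- r = 0.5, f = 0.5 in both arms: 21.0% − 16.5% = 4.5 points (no change from row 12)
- r = 0.5, f at the planned rates: 19.25% − 14.5% = 4.75 points (change 0.25)
- r = 1, f at the planned rates: 15% − 10% = 5.0 points (change 0.5)

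**Unequal loss** (illustration: 12% CT, 8% ETS, half return, half of those fail):

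- Row 12: CT 0.88 × 15% + 12% = 25.2%; ETS 0.92 × 10% + 8% = 17.2%; difference 8.0 points
- Observed data: CT 13.2% + 6% + 3% = 22.2%; ETS 9.2% + 4% + 2% = 15.2%; difference 7.0 points

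Here the choice of rule moves the difference by 1 point.

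**The case against.** The best defence is that the two texts do different jobs: the paragraph says when loss status is settled, and row 12 gives the criterion. The paragraph does not say that loss may be determined only at the end, nor that returners are judged on observed results. Row 12 also keeps the child in the analysis, as a failure. On this view the paragraph's sentence protects children who miss visits without ever meeting row 12.

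Part of this stands. Analysis on observed data is the natural reading of the paragraph, not its wording. A child may also miss a study visit and still be managed through routine clinic care or, in ETS, weekly calls and home visits, so the group in conflict is narrow. But the defence leaves row 12's withdrawal unexplained. Removing a randomised child who is back in clinic fits poorly with intention to treat and with an unqualified 24-month viral load schedule.

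A reader might also infer four stronger things that the protocol does not support:

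- **That one missed visit is enough to trigger row 12.** This depends on a clock start that is not stated.
- **That the imputed failure is dated to the lapse.** No text dates it.
- **That viral loads are certain to be lost.** Row 12 does not say that measurements stop. Returners are back at the clinic, and medical records and laboratory reports are source documents under Data Management. Whether viral loads would be taken there is not stated either way.
- **That the treatment comparison is materially biased.** Under equal loss and return it barely moves, and the protocol gives no evidence of unequal return. Unequal contact by arm makes unequal loss plausible, no more.

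**Conclusion.** The concern holds for a child out of contact for more than 6 months who returns by month 24. Two consecutive missed visits without contact make the case clear. For that child row 12 conflicts with the paragraph above the table and fits poorly with the stated intention to treat. As written, it turns a living and possibly suppressed child into a primary-endpoint failure and puts 1 or 2 scheduled viral loads per such returner at risk.

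The size rests on return and failure rates that the protocol does not give. With 10% loss, the effect on each arm's failure rate runs from about 0.5 points to about 9 points. The upper end needs every lost child to return and to fail at the planned rates, so it is a bound and not an expectation. The between-arm difference moves about 0 to 0.5 points if loss and return are equal by arm, and more if they are not. This is worth correcting because the fix is cheap and uncollected data may not be recoverable, not because a wrong conclusion has been shown.

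**What to change.** In row 12, replace the withdrawal of children who return by month 24 with these rules:

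- The child stays in follow-up in the randomised arm.
- The remaining scheduled viral loads and assessments are taken to month 24.
- Observed outcomes are analysed by allocated arm.
- Loss counts as failure only for children who have not returned by the end of follow-up.

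The cost is a change of wording and continued follow-up for at most about 26 to 27 returners per arm if loss is as planned. Their viral loads are already in the schedule. The clock start, the meaning of managed, and the recording of lapse and return dates would help, but they can be settled in the analysis plan or case report form. Whether returning ETS children rejoin peer support is the investigators' choice and is not needed for this correction.
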